### Randomization and Sample Size Calculation

Enrolled LTBI participants linked to the same index case will be defined as a cluster [14,15], with an assumed average cluster size of 4 participants. Cluster-level randomization will be triggered when ≥1 eligible participant is enrolled within a cluster. Randomization sequences will be pregenerated by the study statistician using SAS (version 9.4; SAS Institute Inc) and will not be accessible to any personnel involved in enrollment, assignment, or intervention delivery. Designated personnel will perform centralized randomization via the interactive web response system. Randomization results will be relayed to the respective site investigators. This is an open-label study, and all participants within the same cluster will receive identical group assignments. To address intercenter heterogeneity, a 2-stage randomization strategy will be applied: in the first stage, stratification by study site will balance baseline characteristics across centers; in the second stage, permuted block randomization (block size=4) within each site will ensure immediate group balance during participant enrollment.

On the basis of surveillance data from China’s National Tuberculosis Control Program, we estimate that the 2-year cumulative active TB incidence among LTBI participants will be 7% [16,17]. Both the 3HR and 1H_3_P_3_ regimens are assumed to have 70% protective efficacy (ie, reducing the 2-year cumulative incidence of active TB into 2.1%).

The intracluster correlation coefficient (ICC) was incorporated into calculations. A systematic review reported ICC values of 0.028 (range 0.0005‐0.21) for school-based clusters [15], while the National Institutes of Health Pragmatic Trials Collaboratory suggested a range of 0.01 to 0.05 [18]. Therefore, we adopted a conservative ICC estimate of 0.05 for this study.

Using these parameters and a prespecified noninferiority margin of a 20% relative reduction in protective efficacy, a total of 396 clusters (n=1584 participants) per treatment arm are required to achieve 80% power at a 1-sided *α*=.05. This sample size is calculated to satisfy the clinically meaningful noninferiority margin, accounting for the cluster randomized design (ICC=0.05, average cluster size=4). Accounting for a 10% attrition rate to mitigate the impact of loss to follow-up on statistical power and outcome validity, each arm will enroll 1760 participants.

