### Statistical Analysis

Statistical analyses will be performed using SAS and R (R Foundation for Statistical Computing). Multiple imputation will be conducted to handle missing data, with additional inverse probability weighting applied for the nonintervention cohort to adjust for potential attrition bias. Continuous variables will be summarized as mean (SD) or median (IQR), as appropriate. Categorical variables will be summarized as counts and percentages.

The primary analysis will assess the noninferiority of the 1H_3_P_3_ regimen compared to the 3HR regimen in preventing active TB over the 24-month follow-up period, and the primary end point is the composite of bacteriologically confirmed or clinically diagnosed active TB. To account for the cluster randomized design and the inherent correlation within clusters, we will use a Cox proportional hazards regression model with shared frailty terms and exact likelihood estimation. Noninferiority of the 1H_3_P_3_ regimen relative to the 3HR regimen will be concluded if the analysis demonstrates that the 1H_3_P_3_ regimen does not experience a ≥20% relative reduction in protective efficacy for preventing active TB over the 24-month follow-up period. To enhance precision and address potential baseline imbalances despite randomization, the model will adjust for key prespecified covariates, such as age, sex, BMI, characteristics of the index case (smear or cavitation status), and cluster size. Outcomes will be assessed via 2 prespecified analyses with explicit definitions: the modified intention-to-treat population includes all randomized participants who received at least 1 dose of the study medication, analyzed by the assigned treatment group regardless of subsequent protocol deviations or treatment discontinuation; the per-protocol population includes all randomized participants who completed ≥90% of scheduled doses within 110% of the planned treatment duration without major protocol deviations (including use of prohibited concomitant anti-TB medications, enrollment despite exclusion criteria, or unblinding to outcome assessors). Prespecified subgroup analyses will examine treatment effect heterogeneity by age (13-17 years vs ≥18 years) and index case features (smear or cavitation status), tested through interaction terms in Cox models (interaction *P*<.10).

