For secondary end points, all AEs, serious AEs (SAEs), and treatment discontinuations due to AEs will be documented. Group differences in AE proportions will be analyzed using the chi-square test or Fisher exact test (2-sided *α*=.05). Treatment completion is defined as consuming ≥90% of planned doses within 110% of the planned treatment duration (≥11 doses within 6 weeks for the 1H_3_P_3_ group and ≥81 doses within 16 weeks for the 3HR group). The 2-year cumulative incidence of active TB in the nonintervention cohort will be calculated using the Kaplan-Meier method, with 95% CI estimated. The protective efficacy of the 1H_3_P_3_ and 3HR regimens relative to the nonintervention cohort will be quantified as the risk reduction rate: 1–(intervention group incidence/nonintervention group incidence). The Fisher exact test will be used to compare incidence differences among the 3 cohorts.

All analyses concerning the PRO end point will be explicitly restricted to the subgroup of participants who complete the EuroQol 5-Dimensions 3-level questionnaire. The baseline characteristics of this PRO subgroup will be compared between the 2 arms to confirm that randomization balance was maintained. Any interpretation of PRO findings will explicitly acknowledge their exploratory nature and the fact that they are derived from a subset of the total study population. Trends in PRO metrics over time will be visualized using line graphs, with mean values and 95% CIs plotted to illustrate group-level changes. A mixed-effects model for repeated measures will be used to compare PRO differences between the 1H_3_P_3_ and 3HR groups across time points, with fixed effects including treatment group, assessment time point, treatment group×time point interaction, age, sex, BMI, and index case cavitation status, and a random participant-specific intercept to account for within-subject correlation from repeated assessments.

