### Quality Assurance

All participating sites are regionally designated medical centers for TB, staffed by experienced clinical teams. Prior to study initiation, all personnel will complete mandatory protocol training, including certification in intervention delivery, data collection standards, and compliance monitoring. Dedicated project managers will provide oversight of drug accountability procedures and on-site auditing to ensure protocol adherence and perform trial conduct monitoring quarterly.

Medication adherence is one of the key assessments for this study. Thus, adherence monitoring uses a 3-strategy verification framework: direct participant reporting during follow-up visits, cross-checking of self-administered medication diaries, and quantitative pill counts of returned drug containers. Within each cluster, peer coordinators will conduct weekly adherence reminders and provide real-time troubleshooting for medication-related challenges.

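### AE proportions, three-cohort TB incidence and the quality-of-life model are analysed as if participants were independent, although treatment is randomised by cluster (secondary and exploratory analyses only)

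*Protocol article*

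**What the plan says.** The section on randomization and sample size defines a cluster as the enrolled contacts of one index case, and "all participants within the same cluster will receive identical group assignments". It assumes 4 participants per cluster and an ICC of 0.05. Under Statistical Analysis, the primary Cox model carries a shared frailty term expressly because of this design.

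The same section then names methods for three further comparisons:

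- AEs: "Group differences in AE proportions will be analyzed using the chi-square test or Fisher exact test", at a 2-sided 5% level.
- TB incidence in the two randomised arms and the nonintervention cohort: "The Fisher exact test will be used to compare incidence differences among the 3 cohorts".
- EQ-5D: a mixed model for repeated measures. Its fixed effects are listed, and the only random effect is "a random participant-specific intercept to account for within-subject correlation from repeated assessments".

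No cluster term, robust variance, GEE or design-effect correction is stated for any of the three. For discontinuation, the section says only that "all AEs, serious AEs (SAEs), and treatment discontinuations due to AEs will be documented". Treatment completion is defined, but no test is named for it.

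**The concern.** Chi-square and Fisher tests take each participant as an independent observation. When whole clusters are allocated and outcomes correlate positively within them, the arm difference varies more than these tests allow. A participant intercept handles repeated measurements on one person. It cannot absorb correlation between classmates, so the standard error of the treatment contrast lacks a between-cluster component.

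The article gives reasons to expect some correlation: shared class or dormitory, open-label treatment, diaries in which participants log AEs, and a support scheme in which "peer coordinators will conduct weekly adherence reminders". Safety, quality of life and stopping because of AEs make up the first secondary objective, and the abstract's conclusion anticipates a well-tolerated regimen. Those are the comparisons whose stated error rate would be off.

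This is not a detail left to a fuller document. The methods are named, and they conflict with the design that the primary analysis respects.

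**Working it through.** **Inputs from the article.** Cluster size m = 4; adopted ICC 0.05; cited ICCs 0.028 (range 0.0005 to 0.21) and 0.01 to 0.05; 396 clusters per arm before attrition. Enrolment to date gives 2478/627 = 3.95 per index case, which supports m of about 4.

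**The plan's own figures.** 396 × 4 = 1584 and 1584/0.9 = 1760 per arm, or 1760/4 = 440 clusters. Both steps reproduce. The 1584 itself does not follow from the stated margin and incidence, but that is a separate matter and does not enter here.

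**Formulas.** Design effect DE = 1 + (m − 1) × ICC. Correct standard error / unadjusted standard error = √DE. True size of an unadjusted 2-sided 5% test = 2 × [1 − Φ(1.96/√DE)].

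**At the plan's values.** DE = 1 + 3 × 0.05 = 1.15; √1.15 = 1.072; 1.96/1.072 = 1.828; true size = 6.8%. An unadjusted 95% interval would cover 93.2%.

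| ICC | DE | Correct SE / unadjusted SE | True size |
|---|---|---|---|
| 0.0005 | 1.0015 | 1.001 | 5.0% |
| 0.01 | 1.03 | 1.015 | 5.4% |
| 0.028 | 1.084 | 1.041 | 6.0% |
| 0.05 | 1.15 | 1.072 | 6.8% |
| 0.21 | 1.63 | 1.277 | 12.5% |

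**Unequal clusters.** With an assumed coefficient of variation of 0.8, DE = 1 + [(1 + 0.8²) × 4 − 1] × 0.05 = 1.278, and the true size at ICC 0.05 is 8.3%.

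**Simulation.** Beta-binomial outcomes, 440 clusters of 4 per arm, no true difference; 8000 runs for chi-square, 3000 for Fisher:

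| Event rate | ICC | Chi-square | Fisher |
|---|---|---|---|
| 2.1% | 0.05 | 6.6% | 4.5% |
| 5% | 0.05 | 6.8% | 6.5% |
| 20% | 0.05 | 7.1% | 7.0% |
| 2.1% | 0.21 | 12.3% | 9.9% |
| 5% | 0.21 | 12.6% | 10.9% |
| 20% | 0.21 | 12.0% | 11.3% |

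The formula holds for chi-square. Fisher's test stays near or below 5% only for rare events at modest ICC.

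**Scope of the figures.** They describe the comparison of the two randomised arms. Decliners also share index cases, so independence fails for the nonintervention cohort too. There, however, one index case can contribute contacts to both sides of the contrast, so the direction of the error is not fixed.

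**The case against.** The strongest reply is that the effect is small and confined. At the ICC the plan itself calls conservative, 5% becomes about 6.8%; at the cited central value it becomes 6.0%. Rare events tested by Fisher may show no inflation. Randomisation is stratified by site, which an unstratified test ignores, so any between-site share of the correlation would work the other way. The EQ-5D and nonintervention comparisons are labelled exploratory. All of this stands, and it limits the severity. It does not make the stated methods fit the design.

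A reader might also infer more than the article supports:

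- *That discontinuation and completion are tested wrongly.* The chi-square/Fisher rule is written for AE proportions. Extending it to AE-related discontinuation is a natural reading but not an explicit one, and no test is named for completion.
- *That all reported intervals are too narrow.* Chi-square and Fisher tests give p-values. The interval point applies to the EQ-5D estimates and to the Kaplan-Meier interval if it is left unadjusted.
- *That AEs cluster more strongly than TB, so that much larger errors apply.* The article gives no ICC for AEs or quality of life, and the peer measures are mainly about adherence. Values above 0.21 have no basis in it.
- *That the three-cohort Fisher test ignores censoring.* Multiple imputation is planned and could supply 24-month status; the article does not say how the two connect.
- *That self-selection of decliners belongs here.* The plan does have "additional inverse probability weighting applied for the nonintervention cohort to adjust for potential attrition bias" and states no weighting for the choice to decline. But that is confounding in an exploratory comparison, a different issue from clustering. Remedying it may need laboratory data that the article does not show decliners to have.

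**Conclusion.** The point holds, at moderate severity, for three named analyses: AE proportions, three-cohort TB incidence, and the EQ-5D mixed model. For the arm comparison of AEs by chi-square, the true size is about 6.8% at m = 4 and ICC 0.05, and between 5.0% and 12.5% over the cited ICC range. It is higher if cluster sizes vary. These figures assume that the ICCs quoted for the sample size carry over to AEs and quality of life, which the article does not establish. The primary noninferiority analysis already allows for clustering, so nothing here puts the trial's main conclusion in doubt.

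**What to change.** - **AEs:** compare proportions with GEE or mixed-effects logistic models, or modified Poisson regression, using the index-case cluster as the grouping unit and including site. Treat AE-related discontinuation the same way if it is to be tested.
- **EQ-5D:** add a random cluster intercept alongside the participant intercept.
- **Three cohorts:** replace the Fisher test with Kaplan-Meier or Cox estimates with cluster-robust standard errors, and report the comparison as exploratory and non-randomised.

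The cost is slightly wider intervals, somewhat larger p-values and some extra programming. The cluster identifier already exists because it drives allocation, and analysis starts only after the 2-year follow-up, so the change can be made in advance without new data.

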## Methods

### Study Design

This is a multicenter, prospective, cluster randomized, noninferiority clinical trial comparing the protective efficacy and safety of the 1H_3_P_3_ regimen with those of the 3HR regimen for TPT in adolescents and adults with LTBI. Prior to trial initiation, close contacts of pulmonary TB index cases within school environments will undergo active screening through the TB-YOUTH Screening program, a cross-sectional study (ClinicalTrials.gov NCT06033807), under the auspices of the National Tuberculosis Control Program in China. After excluding active TB, eligible LTBI participants will be grouped into clusters by their corresponding index cases. The clusters will then be randomized in a 1:1 ratio to receive either the 1H_3_P_3_ or the 3HR regimen for TPT. Medication adherence and adverse events (AEs) will be monitored at week 2, month 1, and month 2 for the 1H_3_P_3_ group, and at week 2 and then monthly until month 4 for the 3HR group after treatment initiation. Participants will undergo follow-up clinical assessments every 6 months for 2 years following randomization. The preventive efficacy of each study arm against active TB will be evaluated at the conclusion of the follow-up period.

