### Follow-Up and Assessments

Participants in both study groups will undergo prospective monitoring comprising two phases: (1) on-treatment assessment (from enrollment to 1 month after treatment completion) and (2) posttreatment assessment (up to 24 months after randomization). On-treatment assessments will involve standardized clinical evaluations, including physical signs, laboratory testing, medication adherence (pill counts and self-reporting), and safety monitoring, and will be scheduled at week 2, month 1, and month 2 for the 1H_3_P_3_ arm, and at week 2, then monthly until month 4 for the 3HR group. On the basis of recommendations from the independent protocol review board, and to comprehensively evaluate the impact of interventions on quality of life, a protocol amendment was implemented after approximately 2300 participants had been enrolled. Following ethics committee approval, the EuroQol 5-Dimensions 3-level questionnaire (version 6.0, December 2018) was incorporated as an exploratory end point. This questionnaire will be administered at every on-treatment assessment for participants enrolled after the amendment’s effective date. Posttreatment assessment will focus on active TB surveillance as well as delayed AE monitoring and will occur every 6 months from randomization until study exit. At each visit, participants will receive a standardized symptom screening for active TB, including persistent cough (≥2 weeks), fever, night sweats, weight loss, hemoptysis, or other TB-associated symptoms. Participants with positive symptom screens will undergo confirmatory sputum culture and molecular diagnostic testing. The end point adjudication committee will determine the final active TB diagnosis per predefined criteria.

The schedule of this study is summarized in Table 2.

**Table 2. T2:** SPIRIT (Standard Protocol Items: Recommendations for Interventional Trials) diagram showing enrollment, intervention, and assessment procedures.

	Enrollment	Allocation	Postallocation phase						Closeout
Time point^a^	–30 days	0 day	2 weeks	1 month	2 months	3 months	4 months	Every 6 months	24 months
Enrollment									
Eligibility screening	✓								
Informed consent	✓								
Medical history	✓								
Allocation		✓							
Interventions									
1-month isoniazid plus rifapentine 3 times weekly regimen		↔^b^	↔	↔					
3-month daily isoniazid plus rifampicin regimen		↔	↔	↔	↔	↔			
Assessments^c^									
Demographic characteristics and medical history	✓	✓							

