Treatment adherence			✓	✓	✓	✓			
Safety monitoring			↔	↔	↔	↔	↔		
Tuberculosis surveillance		↔	↔	↔	↔	↔	↔	↔	↔

a This row displays specific time points relative to randomization. Acceptable time window: more or less than 7 days for the intervention period and more or less than 30 days for the postintervention phase.

b ↔: this arrow represents continuous interventions.

c On-treatment assessments and 1-month posttreatment assessments require in-person attendance, whereas postintervention assessments may be conducted in person or remotely.

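### Adverse event proportions are to be compared by a crude test although the two arms are not monitored equally, with no common window named and clustering ignored

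*Protocol article*

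**What the plan says.** Comparing safety between the regimens is part of the first secondary objective (Study Objectives and End points). The Statistical Analysis section states that all AEs, serious AEs and discontinuations due to AEs will be documented, and then names the test: "Group differences in AE proportions will be analyzed using the chi-square test or Fisher exact test", at two-sided 0.05. It mentions no observation window, exposure adjustment or cluster adjustment for this comparison.

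The visit schedule appears in two places. Study Design gives three time points for the short regimen, "at week 2, month 1, and month 2 for the 1H_3_P_3_ group". The comparator has five visits over a longer period; its monitoring takes place "at week 2 and then monthly until month 4 for the 3HR group after treatment initiation". Follow-Up and Assessments ties this phase to regimen length, "on-treatment assessment (from enrollment to 1 month after treatment completion", and includes laboratory testing in it. Note c of Table 2 requires these visits to be in person.

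AE collection does not end there. "Posttreatment assessment will focus on active TB surveillance as well as delayed AE monitoring and will occur every 6 months from randomization until study exit". This applies to both arms, but note c of Table 2 says that "postintervention assessments may be conducted in person or remotely".

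**The concern.** A crude proportion treats every participant as having had the same chance of having an AE recorded. Here that chance differs by arm. Between month 2 and month 4 a 3HR participant has two scheduled in-person visits with laboratory tests, and a 1H3P3 participant has none. A short illness or a passing laboratory abnormality at month 3 is likely to be recorded in the first case and may go unrecorded in the second, even if it has nothing to do with either drug.

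The direction is known: unequal detection lowers the 1H3P3 proportion relative to 3HR. The article's conclusions look ahead to a well-tolerated short regimen, and this comparison would support that wording. Separately, participants sharing an index case are randomized together. The primary model allows for that through shared frailty, but a chi-square or Fisher test treats participants as independent.

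**Working it through.** The article states no AE rate and no power for the AE comparison, so there is no figure of its own to reproduce.

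**Inputs from the document**
- Active AE visits: 1H3P3 at week 2, months 1 and 2 (3 visits); 3HR at week 2, months 1, 2, 3 and 4 (5 visits).
- Participants per arm: 396 × 4 = 1584, and 1584 / 0.90 = 1760 enrolled.
- Intracluster correlation 0.05 and cluster size 4, so the design effect is 1 + (4 − 1) × 0.05 = 1.15. The correlation was chosen for the sample size calculation; using it for AEs is an assumption.

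**Assumptions not in the document, equal in both arms**
- q: probability of a drug-caused AE.
- λ: background AE rate per month.
- s: share of the 1H3P3 arm's month 2-4 background AEs that later visits recover.

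**Formulas**
- 1H3P3: p1 = 1 − (1 − q) exp(−λ(2 + 2s)). 3HR: p2 = 1 − (1 − q) exp(−4λ).
- Rejection probability: normal approximation to the two-sided 5% two-proportion test, 1760 per arm, participants treated as independent.

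**One case in full** (q = 10%, λ = 2% per month, s = 0)
- p1 = 1 − 0.9 × exp(−0.04) = 13.5%; p2 = 1 − 0.9 × exp(−0.08) = 16.9%; difference 3.39 points.
- Pooled proportion 15.2%, standard error 0.0121, critical difference 1.96 × 0.0121 = 0.0237.
- (0.0339 − 0.0237) / 0.0121 = 0.84, so the rejection probability is 0.80. Drug harm is the same in both arms.

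**By recovery share, q = 10%**

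| Background rate | s = 0 | 25% | 50% | 75% | 100% |
|---|---|---|---|---|---|
| 1% per month | 0.34 | 0.21 | 0.12 | 0.07 | 0.05 |
| 2% per month | 0.80 | 0.54 | 0.27 | 0.10 | 0.05 |
| 5% per month | >0.99 | 0.98 | 0.74 | 0.25 | 0.05 |

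**By drug harm, s = 0.** With q = 0, rejection is 0.93 at 1% per month (2.0% versus 3.9%) and above 0.99 at 2% per month (3.9% versus 7.7%). With q = 20% it is 0.20 and 0.55. Over q from 0 to 20% and λ from 0.5% to 10% per month, it runs from 0.09 to 1.00, and the expected difference always favours 1H3P3.

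**Visit count alone.** If each visit has a 1% chance of a new finding, 1 − 0.99³ = 3.0% against 1 − 0.99⁵ = 4.9%, and rejection is 0.84.

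**Clustering.** If the design effect of 1.15 applies to AEs, a test that ignores it has a true two-sided level of 2 × [1 − Φ(1.96 / √1.15)] = 2 × [1 − Φ(1.828)] = 6.8% instead of 5%, even with perfectly equal monitoring.

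**The case against.** The strongest reply is that AE collection does not stop at month 2 in one arm and month 4 in the other. A reader might infer from the visit schedule that AE proportions are counted over 2 months against 4. The document does not say so: delayed AE monitoring runs every 6 months to study exit in both arms, and the safety row of Table 2 runs to month 4 without separating the arms. The analysis window is simply not stated. This stands, and it is why the point concerns unequal ascertainment rather than unequal windows. It does not remove the problem. After month 2, the next scheduled contact for 1H3P3 is at month 6, possibly remote, and would have to recover events up to four months old.

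A second reply is that the reporting window and exposure-adjusted rates are commonly left to the SAP. That is fair for the omissions alone. But the article itself fixes both the unequal schedule and the crude test, and their combination is the issue.

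Third, AEs caused by two further months of drug are a real difference between the regimens. That also stands. The distortion is limited to background events and unequal detection, and the whole-regimen proportion remains a fair description of burden. Serious AEs and deaths depend less on visit count and are less exposed.

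A reader might also infer that the test is almost certain to declare 1H3P3 safer, or that it would hide a 1H3P3 excess of some 4 to 9 percentage points. Those figures need no drug-caused AEs in the first case and no later recovery in either. The documents support neither assumption.

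**Conclusion.** The concern holds as one of unequal ascertainment. The schedule gives 3HR two more in-person visits with laboratory tests, the named test is a crude comparison of all-AE proportions, no common window is given and clustering is ignored. The bias favours 1H3P3 and could produce an apparent safety advantage from background events.

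Its size cannot be fixed from the document. Under equal drug harm, rejection ranges from the nominal 5% if later visits recover every missed event to nearly 100% if they recover none and background rates are high. These figures rest on assumed rates, constant background risk and the normal approximation. The primary end point is not affected. The change is worth making because a named secondary objective is open to bias in a known direction.

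**What to change.** Keep the whole-regimen AE proportion, label it as regimen burden, and test it with a method that accounts for clusters, for example generalized estimating equations or mixed logistic regression. Add beside it:

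- **(a)** A comparison over months 0-2, where both arms have the same visits, with a note that it omits the last part of 3HR treatment.
- **(b)** Exposure-adjusted rates as a sensitivity analysis, noting that the share of observed time on drug differs: 1 of 2 months against 3 of 4 if counted to the end of the on-treatment phase.
- **(c)** Separate comparisons of drug-related AEs and of grade 3 or higher AEs.

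Neither (a) nor (b) is neutral enough to replace the whole-regimen comparison. State the observation window for each table, and do not rest a claim of better safety on the crude all-cause proportion alone.

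Onset date, severity and causality are already recorded, so no new data are needed. The cost is SAP wording and a few more tables, and the apparent advantage of 1H3P3 may turn out smaller.
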